### Phase 2: Intervention Development

We will use intervention mapping [24] and the designing for dissemination [25] approach, which will be informed by data from the first phase, to develop the intervention. We chose the 4-step intervention mapping model to inform the development process [24]. Intervention mapping is a systematic, iterative process characterized by contextual evaluation, stakeholder feedback, and the use of theories and evidence, making it an excellent fit for implementation science trials in real-world settings [24]. Using intervention mapping will allow us to prioritize key targets while considering barriers to testing and prevention.

The tablet-based intervention will include 3 modules consisting of multiple subtopics, deliver tailored (ie, for youth and rural contexts) digital content in the clinic waiting room, include motivational interviewing [26] components that are effective in evoking behavior change while being acceptable to adolescents and parents, and include ongoing support through text reminders. The intervention will be designed to reduce health provider burden and to consider practice and environmental limitations. We anticipate drafting 2 to 3 versions of the intervention before finalizing a version for pilot-testing. Each version will be reviewed by a group of adolescents and clinical health providers (estimated number of reviewers per version: range 4-6).

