**Figure 2 figure2:**
[figure not shown]
Randomized controlled trial study flow (phase 3).

All participant data collection will occur electronically. Informed consent will be collected via Adobe Sign (Adobe Inc), and self-report data will be collected through a standardized Qualtrics (Qualtrics International Inc) survey. Pre- and postintervention data collection, which will occur in clinics, will be conducted with iPads (Apple Inc) that are dedicated to the study site. Data will be immediately uploaded to a secure database through wireless connectivity. Self-report data to be collected at 2 and 6 months post intervention will be captured by using the same standardized Qualtrics survey that will be used in clinics; the direct survey link will be shared via text or email, depending on the participants’ preferences.

We will conduct exit interviews with clinic health providers to assess barriers and facilitators to implementation specifically to inform regional dissemination.

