### Effectiveness Data

Data on clinic-level vaccination rates and vaccination series completion rates will be collected prior to the start of the study and once per year thereafter. Patient-specific data will be collected at the end of the 6-month study cycle.

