### Medical Records

We propose to collect data on vaccination from medical records at partner clinics. We will request records from partner clinics, and a member of each clinic will extract them for evaluation. The research team will review medical records for evidence that participants accepted vaccination during the 6-month study period, as well as evidence of whether the participants completed the vaccine series.

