### Phase 3: Data Management and Quantitative Analysis

A descriptive analysis of all study feasibility and outcome variables will be summarized by using means and SDs for continuous measures and frequencies and percentages for categorical measures. Between-group differences will be compared by using standard 2-tailed cluster analyses. Further, 2-sample tests for proportions [28] will be used to compare initial vaccination acceptance, the indication of dose completion, and study dropout. An adjusted McNemar test [29] will be used to determine if the intervention group had any changes in vaccine knowledge post intervention. Similar analyses will be used in the control group, and the two groups’ changes will be examined. For any continuous measure (eg, stigma), 2-sample *t* tests [30] will be used, and appropriate assumptions will be validated. Factors related to unexpected design or study implementation issues, such as systematic enrollment issues at clinics or differential times between patients’ first visit and their follow-up resulting from issues beyond common follow-up issues, will be assessed. If it is determined that these issues require analysis adjustment, we will use generalized estimating equations to compare group differences in all measures while adjusting for these factors. Generalized estimating equations require all missing data to be missing completely at random; however, as our primary outcome relates to initial vaccination acceptance, we do not expect any missingness. Likewise, we will assume that study dropout is an indicator of incomplete dosing. Missing values for other outcomes will be examined, and if missingness at random can be assumed, multiple imputations [31] will be used.

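### The rule that study dropout means incomplete dosing is not limited to participants without a record, although series completion is read from clinic records

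*Protocol article*

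**What the plan says.** Three parts of the protocol article bear on this point.

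- **Source of the outcome.** The Medical Records section says: "We propose to collect data on vaccination from medical records at partner clinics". It continues: "We will request records from partner clinics, and a member of each clinic will extract them for evaluation". The research team reviews these records for acceptance of vaccination during the 6-month period, "as well as evidence of whether the participants completed the vaccine series". The Effectiveness Data section adds the timing: "Patient-specific data will be collected at the end of the 6-month study cycle".
- **What follow-up asks of the participant.** The text under Figure 2 in Phase 3: Intervention Evaluation describes remote questionnaires: "Self-report data to be collected at 2 and 6 months post intervention will be captured by using the same standardized Qualtrics survey". The links go out by text or email.
- **The analysis rule.** Phase 3: Data Management and Quantitative Analysis says that no missingness is expected for the primary outcome, initial acceptance, and goes on: "Likewise, we will assume that study dropout is an indicator of incomplete dosing". The same section says that two-sample tests for proportions "will be used to compare initial vaccination acceptance, the indication of dose completion, and study dropout".

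The article does not define study dropout. It does not say that the rule applies only where no record can be obtained.

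**The concern.** Completion is a measured outcome with its own data source. A participant who stops answering survey links still has a clinic record, and that record shows whether the series was completed. The analysis rule assigns an assumed value to dropouts with no exception for those whose completion is documented. Followed literally, it replaces data with an assumption.

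The reasoning in the analysis section is also uneven. Acceptance and completion come from the same record review, yet acceptance is expected to be complete while completion is imputed from dropout. Dropout and completion are then tested as separate outcomes, although the rule makes one partly determine the other.

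At stake is the completion comparison. The abstract says that the pilot looks for a signal of effectiveness, and Table 1 lists effect size estimation under limited efficacy testing. A completion difference that partly reflects retention would be a poor basis for planning a later trial.

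**Working it through.** The article states no dropout rate, expected completion rate, effect size or power, so there is no figure of its own to reproduce. The size of the problem can only be illustrated.

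**Inputs from the article.** There are 120 participants in 4 clinics, 2 clinics per arm (Phase 3: Intervention Evaluation), and tests are two-tailed. The Background gives a series completion rate of about 20% for Alabama. That is a population rate, not a forecast for youth who are unvaccinated at entry and followed for 6 months.

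**Assumptions.** 60 participants per arm; alpha 0.05; dropout between 0% and 30%; true completion between 5% and 40%; dropout unrelated to completion; clustering ignored.

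**Formula.** Let p be true completion and d the dropout rate. Under the rule, only completers who stay in the study count:

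recorded completion = p × (1 − d)

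If dropout is related to completion, d is the dropout rate among true completers. If no completer drops out, the error is zero.

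**No true effect, dropout 10% in one arm and 30% in the other.** The false difference is p × (0.30 − 0.10).

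| True completion, both arms | Recorded, 10% dropout | Recorded, 30% dropout | False difference | Participants per 60 |
|---|---|---|---|---|
| 5% | 4.5% | 3.5% | 1 point | 0.6 |
| 10% | 9% | 7% | 2 points | 1.2 |
| 20% | 18% | 14% | 4 points | 2.4 |
| 40% | 36% | 28% | 8 points | 4.8 |

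At 20% true completion there are 120 × 0.20 = 24 true completers, of whom 60 × 0.20 × (0.10 + 0.30) = 4.8 are miscoded. Exact enumeration of the pooled two-sample z-test gives a rejection rate of 8.7% at 20% completion and 15.8% at 40%, against about 5% without dropout.

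**No true effect, equal dropout.** Both rates fall but the difference stays at zero. At 20% and 40% true completion with 10% to 30% dropout, the rejection rate stays between 4.7% and 5.3%.

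**True effect, 40% intervention against 20% control.**

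| Dropout, intervention / control | Recorded rates | Difference | Power (normal approximation) |
|---|---|---|---|
| 0% / 0% | 40% / 20% | 20 points | 67% |
| 20% / 20% | 32% / 16% | 16 points | 54% |
| 30% / 10% | 28% / 18% | 10 points | 25% |
| 10% / 30% | 36% / 14% | 22 points | 80% |

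The rule can therefore shrink or inflate the difference. If completion is scored from the record for everyone, the first row applies whatever the survey attrition.

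**The case against.** The strongest reply is that the sentence stands in a discussion of missing data. Read there, it may mean only that a participant whose completion status is unknown is counted as incomplete, while the record is used wherever it exists. The Medical Records section would then be fully compatible with it. This reading is possible, and a reader should not infer that the investigators have decided to overrule documented doses. But the rule is not limited in that way, and someone applying it as written would score a documented completer as a failure.

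A second reply is that dropout need not mean survey non-response. That stands in part. The term is undefined, and a participant who withdraws permission for record review has no usable outcome. Since the follow-up contacts described are surveys, survey attrition is the natural reading but not the only one.

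A third concerns direction. The intervention is to "include ongoing support through text reminders", and a reader might infer that retention will be better in that arm and the bias will favour it. The article does not support this. The control is a time-attention condition, survey links are sent by text or email according to participants' preferences, and no retention figure is given. The direction is open.

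Finally, dropout will itself be compared between arms, so an imbalance would be seen. That helps interpretation but does not correct the completion estimate.

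**Conclusion.** The point holds: a stated rule, applied as written, gives wrong completion values for dropouts who finished the series, although their true status is due to be collected. It should be fixed, but it does not undermine the trial.

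Its size depends on inputs that the article does not supply. With the assumed dropout of 10% against 30% and no true effect, the false difference is 1 to 2 points if true completion is 5% to 10%, and 4 to 8 points if it is 20% to 40%. It is smaller if few completers drop out. The rejection rates and powers also rest on 60 per arm and ignore clustering, so they are indicative only.

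A reader might infer that the trial's main result is at risk. It is not: the rule concerns series completion and the effect-size estimate taken from it, whereas the article names initial acceptance as its primary outcome.

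**What to change.** Replace the sentence with a rule along these lines: series completion is scored from the clinic medical record for every enrolled participant, whatever their survey status; it is missing only where no record is accessible, for example because permission was withdrawn; counting dropouts as incomplete is a sensitivity analysis. Define study dropout in the same place, separating survey non-response from withdrawal of permission for record review.

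The cost is a few sentences in the analysis section, because the clinic records are already to be extracted. The one thing to confirm is that consent allows record review after a participant stops answering surveys; the consent text is not available here, so it may already do so. Checking outcomes against the immunization registry would be an optional addition. The Recruitment section names the registry only for eligibility screening, so its use for outcomes would be a new procedure.

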## Results

The study was funded at the end of December 2020. Approval from the University of Alabama at Birmingham Institutional Review Board was obtained in May 2021, and the qualitative data collection process outlined in the first phase of this project concluded in November 2021. The entire study is expected to be complete at the end of December 2023.

## Discussion

### Study Implications

Based on prior research with rural African American adolescents and their families and given the low rates of vaccination in rural Alabama, developing an intervention to promote vaccination among 15- to 26-year-old youth has the potential to make a notable public health impact. A novel feature of this study is its emphasis on adolescent decision-making and autonomy. This departure from prior studies that focused on changing parental or guardian behavior makes our protocol unique, and we hope that this increases its chances of making a strong impact. Furthermore, by developing this intervention, which leverages existing infrastructure, we increase the likelihood of this intervention being scalable to similar clinic settings across similar rural communities in Alabama and extending into other neighboring states, such as Mississippi and Tennessee.

### Limitations

We note some important limitations to the study. Currently, the intervention focuses on adolescents and does not focus on parents. Because adolescents can consent for their own health care at 14 years of age in the state of Alabama, we opted to focus on them instead of their parents. During the qualitative phase, we may learn about clinic features that indicate a poor fit for such a research trial. If this occurs, as we have ample credibility with rural clinics across the state, we can recruit a replacement facility.

## Abbreviations

HPV: human papillomavirus
IMB: Information-Motivation-Behavioral Skills
